#### Treatment planning

The treatment planning must be carried out on a 3D system with tissue heterogeneity correction and matrix resolution of 2.5 mm. Techniques in the supine position are allowed and the prone position is not allowed.*Breast* Tangent beam pair arrangement to encompass the whole breast is recommended, intending to minimize the total dose in the ipsilateral lung and heart. The treatment plan can be optimized with any dose compensation system, (virtual edges, mechanical wedges, automatic wedges, field-in-field IMRT and steep and shoot or sliding windows IMRT). The treatment will be performed with photons of 6 MV–15 MV. The isocenter will be located within the breast PTV in the experimental group and may be located outside the PTV if the single isocenter technique is being used in the control group. To minimize irradiated ipsilateral lung and heart volumes, collimator rotation and shield with multileaf collimator is allowed.*Tumour bed* Photons or electrons are allowed. Mini-tangential photon fields or single electron field (also mixed energies) can be utilised. The use of boluses can be considered if needed. Simultaneous integrated boost brachytherapy or intraoperative irradiation is also allowed if the dose contribution to the nodal areas can be calculated. The bolus can be used. The dose and fractionation choice is left at the discretion of the treating physician.*Node areas* In the control group, the treatment planning must be optimized to ensure that the nodal areas receive the prescribed dose (except for the internal mammary chain), minimizing the dose at the organs at risk. High tangent, AP/PA, conformational 3D and IMRT techniques are allowed. In the experimental group, treatment planning for nodal areas is not performed. The internal mammary chain will not be irradiated intentionally in any case.

An unplanned gap of up 3 days is acceptable. Longer non-planned interruptions should be compensated by hyperfractionation of the daily normal dose.

#### Dose prescription

All doses prescribed will follow the International Commission on Radiation Units and Measurements guidelines. A minimum of 95% of the volume must receive at least 95% of the prescribed dose. Less than 5% of the volume may receive a dose of 105% and less than 2% should receive a dose of 107%, with a maximum overall dose of 110%. The dose in the breast must be 50.0 Gy by 25 fractions of 2.0 Gy in 5 weeks or through hypofractionated schedules as 40.05 Gy in 15 fractions of 2.67 Gy for 3 weeks. In the tumour bed, the schedule and total dose are left to the centre’s criteria. In node areas, the intentional irradiation to the breast and tumour bed will be calculated. Limiting doses for the organs at risk must be: (1) ipsilateral lung: V20 less than 25%; and (2) heart: V20 less than 10% and V40 less than 5%.

#### Radiotherapy verification

Verification methods will be conducted in both arms. Treatment verification is required at the first treatment fraction and allowed on the three first fractions. The verification must be performed using electronic portal images of the treatment beam; either with MV or kV. Orthogonal images or cone-beam images can be used on the verification of the isocentre. Weekly control will be performed, and systematic daily control is also allowed.

### Follow-up

Patients will be followed for up to 5 years after the intervention according to the visit schedule detailed in Table 1. In each visit, a physical examination and recurrence assessment will be performed. An image assessment will be requested every year after the intervention. Reasons for discontinuing follow-up must be reported.

**Table 1 Tab1:** Schedule of visits and assessments (dots) that will be performed during the 5-year follow-up period

Post-intervention (year)	1					2		3		4		5	
Post-intervention (month)	1	3	6	9	12	18	24	30	36	42	48	54	60
Acute toxicity	●												
Physical exam	●	●	●	●	●	●	●	●	●	●	●	●	●
Image evaluation of local recurrence					●		●		●		●		●
Survival and disease recurrence	●	●	●	●	●	●	●	●	●	●	●	●	●
Chronic toxicity	(Continuous recording)												
Co-medication, (adjuvant)	(Continuous recording)												

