## Methods/design

### Study design

The OPTIMAL study is an open-label multicentre and international trial (NCT02335957) conducted in over 40 sites in Spain, Portugal, and Italy. Eligible patients will be randomized with a 1:1 allocation ratio to receive irradiation on breast, tumour bed, axillary and supraclavicular lymph node areas (intentional arm) or only on breast and tumour bed (incidental arm), as depicted in Fig. 1. Randomization by blocking within centres to minimize imbalance of treatments among centres will be performed using the online randomization software RANDI2 (www.dkfz.de; Heidelberg University) embedded in the electronic case record form (eCRF). All patients will have to provide their Informed Consent prior to the inclusion in the study.

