### Data collection and analysis

#### Data collection

The study data will be recorded in an eCRF (OpenClinica®, LLC). The demographic and clinical data requested is depicted in Table 2. Acute and chronic toxicity will be recorded according to the Common Terminology Criteria for Adverse Events v4.0 (CTCAE) [24] criteria. Specific follow-up outcomes will be assessed and registered during the visits scheduled as stated in Table 1.

**Table 2 Tab2:** Data collected in the electronic case record form

Panel in eCRF	Data recorded
Informed consent	Date
I/E criteria	Yes; not
Demographic data	Age at inclusion; Menstrual State
Comorbidities	If yes: specify
Cancer Histology and Receptors, SLN OSNA	Tumour grade; Tumour size (maximum diameter); P53 (%); Ki67 (%); Lymphovascular infiltration; Ductal Ca in situ; % Estrogenic receptors; % Progesterone receptors; HER2 receptor status; OSNA TTL of SLN
Previous medication (Adjuvant therapy)	Drug; Start date; Stop date
Type of surgery	Tumour surgery; date; Margins
Randomization	Treatment randomly allocated; Randomization date
Radiotherapy intervention	Patient completed the allocated treatment (If no: main reason); Start date; End date; Treatment gaps (If yes, reason); Dose per volume (Mean; Median; D95; D5; Volume) in the breast, tumour bed, supraclavicular and axillary levels I-III, and Internal mammary chain
Co-medication	Drug; Start date; Stop date
Survival and disease recurrence	Date of follow-up visit (If not performed, reason); Local recurrence; Regional recurrence (If yes: nodal level); Distant recurrence (If yes: organ); Vital status (if dead: date and cause)
Image evaluation of local recurrence	Technique; Local recurrence (if yes: Maximum diameter)
Physical examination^a^	Palpable breast tumour (if yes: size, skin infiltration, inflammatory carcinoma, satellite lesions); Palpable axillary nodes (if yes: size); Palpable supraclavicular nodes (if yes: size); Node staging
Acute and chronic toxicity	CTCAE term; Grade; Start date; Stop date; Status (recovered w/o sequels; death)

*eCRF* electronic case record form, *OSNA* One-Step Nucleic Acid Amplification, *TTL* total tumour load, *SLN* sentinel lymph node, *CTCAE* Common Terminology Criteria for Adverse Events

^a^Physical examination is conducted at follow-up visits. It is also addressed at baseline and radiotherapy sessions to confirm the compliance of eligible criteria. If suspicious LNs are detected, the patient will discontinue the study

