#### Statistical analysis

Two sets of patients will be analysed: the intention-to-treat (ITT) group, which includes all randomized patients, to describe the baseline clinic-pathological patients’ characteristics; and the per-protocol subset, which includes patients who finish the intervention treatment as planned with all dosimetry data completed, for the endpoint. A descriptive analysis will be carried out reporting absolute and relative frequencies for all variables recorded and stratified by treatment group. Two analyses of the primary endpoint (disease-free survival rate) will be conducted. The confirmatory analyses will be carried out using a non-inferiority long-rank test in the ITT set of patients, which includes all randomized patients regardless of whether the treatment or follow-up are accomplished. A secondary explanatory analysis will be conducted in the per-protocol subgroup, which will include patients who will have finished the intervention treatment with all dosimetry data completed, by an adjusted Cox regression model using the covariates: centre, age at inclusion, tumour size, hormone receptor status, Her2 receptor status, and OSNA results. With regards to the secondary endpoints: the outcomes of loco-regional and distant recurrence will be analysed using the Cox approach, this time in the ITT set. Acute toxicity will be analysed by a chi-squared test comparing frequencies in both treatment groups. Chronic toxicity will be analysed by using Kaplan Meier curves and comparing them by a standard log-rank test. Interim analyses are planned when 85 events and 169 events will be reached.

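### Chronic toxicity has no marked visit assessment and no listed prompt, so in an open-label trial its detection and onset dates may differ by arm

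*Protocol article*

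**What the plan says.** All references are to the protocol article.

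- **Secondary endpoints.** Chronic toxicity is one of five. Acute toxicity is listed separately.
- **Follow-up, Table 1.** The caption defines the dots: "Schedule of visits and assessments (dots) that will be performed during the 5-year follow-up period". Acute toxicity has one dot (month 1). Physical examination and recurrence each have 13. The chronic toxicity row has none: "Chronic toxicity (Continuous recording". Co-medication has the same entry.
- **Follow-up, text.** "In each visit, a physical examination and recurrence assessment will be performed". Toxicity is not named.
- **Data collection, text.** "Specific follow-up outcomes will be assessed and registered during the visits scheduled as stated in Table 1".
- **Data collection, Table 2.** The physical examination panel covers palpable breast tumour and then "Palpable axillary nodes (if yes: size); Palpable supraclavicular nodes (if yes: size); Node staging". A separate panel for acute and chronic toxicity holds "CTCAE term; Grade; Start date; Stop date; Status (recovered w/o sequels; death".
- **Table 2, footnote.** Physical examination also takes place at baseline and at radiotherapy sessions, to confirm eligibility.
- **Study design.** "The OPTIMAL study is an open-label multicentre and international trial".
- **Statistical analysis.** "Chronic toxicity will be analysed by using Kaplan Meier curves and comparing them by a standard log-rank test".

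**The concern.** A time-to-event comparison needs two things from every patient: the date on which an event was first present, and knowledge that it was absent before then. An open log supplies the first only when someone thinks to make an entry, and it does not supply the second. With no marked assessment and no listed item, the site decides whether to ask about limb swelling, shoulder movement, fibrosis or lung effects.

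The sites are unblinded. Staff who know that the axilla and supraclavicular fossa were treated have more reason to ask about the arm and shoulder. More looking finds more events, and finds them earlier. The log-rank test cannot tell that from a real difference between the arms.

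Every patient has also had breast surgery and sentinel-node assessment. The endpoint is worded as toxicity induced by radiation, but the article lists no toxicity grade before radiotherapy against which later findings could be judged.

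**Working it through.** **Step 1. Set the schedule beside the analysis.**

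| Outcome | Marked visits in Table 1 | Fields listed in Table 2 | Planned comparison |
|---|---|---|---|
| Recurrence | 13 | local, regional, distant, each answered | log-rank for DFS, Cox for recurrence |
| Acute toxicity | 1 (month 1) | open CTCAE log | chi-squared |
| Chronic toxicity | 0 | open CTCAE log | Kaplan-Meier, log-rank |

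The Data collection text sends the reader to Table 1 for when outcomes are assessed, and Table 1 gives chronic toxicity no visit. Table 2 does record the date of each follow-up visit and the reason if it was not held. A missed visit can therefore be told from an attended one. The ambiguity lies in the attended visit with no toxicity entry.

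**Step 2. Is there a figure in the plan to reproduce?** No. The Sample size section says that 1,400 patients are enough to evaluate toxicity differences, but gives no toxicity rate or difference. Current status gives 48 chronic toxicity events among 451 recruited patients. That is 48/451 = 10.6% if there is one event per patient, but it is not split by arm or by follow-up time, so it shows neither under-recording nor a difference in recording.

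**Step 3. Illustrate what unequal detection could do.** All true rates and detection rates here are assumptions. Inputs from the article: 1,400 patients allocated 1:1, so n = 700 per arm, ignoring dropout. The test is taken as a two-sided 0.05 comparison of simple proportions, a stand-in for the log-rank test.

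Observed rate = true rate × detection. With observed rates p1 (intentional) and p2 (incidental), d = p1 − p2 and p̄ their mean:

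- se0 = √(p̄(1 − p̄) × 2/700)
- se1 = √(p1(1 − p1)/700 + p2(1 − p2)/700)
- chance of a significant result favouring the incidental arm = Φ((d − 1.96 × se0)/se1)

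Equal true rate of 15%, detection 80% v 60%:

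- p1 = 0.15 × 0.80 = 0.12; p2 = 0.15 × 0.60 = 0.09; d = 0.03
- se0 = √(0.105 × 0.895 × 2/700) = 0.01639; se1 = 0.01637
- Φ((0.03 − 0.03212)/0.01637) = Φ(−0.13) = 0.45

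| True rate, both arms | Detection, intentional v incidental | Observed | Chance (nominal 2.5%) |
|---|---|---|---|
| 15% | 70% v 65% | 10.5% v 9.75% | 7% |
| 10% | 90% v 80% | 9% v 8% | 10% |
| 20% | 90% v 80% | 18% v 16% | 17% |
| 10% | 90% v 70% | 9% v 7% | 28% |
| 20% | 90% v 70% | 18% v 14% | 53% |
| 15% | 80% v 60% | 12% v 9% | 45% |

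If only the share remaining after 5% yearly dropout counts (1,400 × 0.95^5 / 2 = 542 per arm), the last row falls to 36%.

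**Step 4. Illustrate equal under-detection.** With assumed true rates of 20% v 15% and 700 per arm, power is 69% with full detection, 58% when 80% of events are found (16% v 12%) and 45% when 60% are found (12% v 9%). Real differences would be missed even without bias.

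**The case against.** Several points on the other side stand.

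- **Importance of the endpoint.** A reader might infer that late toxicity is what must justify the lighter treatment. The article does not say so. The primary endpoint is non-inferiority in DFS, chronic toxicity is one of five secondary endpoints, and acute toxicity, another of them, has a scheduled visit. The Abstract promises a comparison of toxicity, not a reduction.
- **Passive reporting.** A reader might take continuous recording to mean spontaneous reports only. The article does not say that either. Patients in both arms are examined at the same 13 visits, and the toxicity panel takes any CTCAE term with grade and dates, so an arm or shoulder event can be entered there. How toxicity is elicited may be set out in the full protocol or the case record form manual, neither of which is shown.
- **The analysis.** A reader might conclude that every patient without an entry is counted as assessed and event-free. The article names the method and no more; event definition and censoring may be in an analysis plan.
- **Baseline.** Table 1 covers the time after the intervention, so a pre-radiotherapy rating would not appear there. A baseline examination and a comorbidities panel exist, though neither is a toxicity grade.
- **Size.** The detection rates are invented, and the mildest case moves the observed difference by only 10.5 − 9.75 = 0.75 points.

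The core remains. The article prints both the schedule and the contents of the record form. It gives acute toxicity a visit and chronic toxicity a different entry, and it lists tumour items but no late-effect items. That is a stated method, not a detail lost in condensation.

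**Conclusion.** The point holds as a low-cost improvement to a secondary endpoint. As stated, chronic toxicity has no marked assessment and no listed prompt, and a blank at an attended visit has two possible meanings. Because the trial is open-label, detection and onset dates may differ by arm, and the plausible direction favours the incidental arm.

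Neither the direction nor the size is documented. The figures of 7% to 53% rest on assumed detection gaps of 5 to 20 percentage points, assumed equal true rates of 10% to 20%, 700 patients per arm and a simple comparison of proportions. They show that a modest gap would matter, not that one exists. The 48 events reported so far are no evidence either way. The point does not touch the DFS comparison, and it does not establish that a toxicity result from this trial would lack credibility.

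**What to change.** 1. In Table 1, mark a chronic toxicity assessment at the existing follow-up visits after the acute period.
2. At each, complete a short fixed list of CTCAE v4.0 terms, identical in both arms, with an explicit grade 0. Candidate items are limb oedema, shoulder movement, breast fibrosis, lung effects, brachial plexopathy and cardiac effects; the study team should settle the list.
3. Keep continuous recording for all other terms.
4. For patients not yet treated, add the same rating at the existing baseline examination.
5. Report chronic toxicity separately for patients enrolled before and after the change, as a sensitivity analysis.

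**Cost.** One form page and a few minutes per visit; no new visits. At the reported status, 1,400 − 451 = 949 patients (68%) remained to be recruited and could follow the full schedule. Those already recruited could join at their remaining visits, with mixed ascertainment and no pre-radiotherapy rating. An event defined as worsening from baseline therefore cannot be computed for them, and should not become the sole definition. The same unblinded staff would complete the list, so open-label bias is reduced, not removed.

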### Data collection and analysis

#### Data collection

The study data will be recorded in an eCRF (OpenClinica®, LLC). The demographic and clinical data requested is depicted in Table 2. Acute and chronic toxicity will be recorded according to the Common Terminology Criteria for Adverse Events v4.0 (CTCAE) [24] criteria. Specific follow-up outcomes will be assessed and registered during the visits scheduled as stated in Table 1.

**Table 2 Tab2:** Data collected in the electronic case record form

Panel in eCRF	Data recorded
Informed consent	Date
I/E criteria	Yes; not
Demographic data	Age at inclusion; Menstrual State
Comorbidities	If yes: specify
Cancer Histology and Receptors, SLN OSNA	Tumour grade; Tumour size (maximum diameter); P53 (%); Ki67 (%); Lymphovascular infiltration; Ductal Ca in situ; % Estrogenic receptors; % Progesterone receptors; HER2 receptor status; OSNA TTL of SLN
Previous medication (Adjuvant therapy)	Drug; Start date; Stop date
Type of surgery	Tumour surgery; date; Margins
Randomization	Treatment randomly allocated; Randomization date
Radiotherapy intervention	Patient completed the allocated treatment (If no: main reason); Start date; End date; Treatment gaps (If yes, reason); Dose per volume (Mean; Median; D95; D5; Volume) in the breast, tumour bed, supraclavicular and axillary levels I-III, and Internal mammary chain
Co-medication	Drug; Start date; Stop date
Survival and disease recurrence	Date of follow-up visit (If not performed, reason); Local recurrence; Regional recurrence (If yes: nodal level); Distant recurrence (If yes: organ); Vital status (if dead: date and cause)
Image evaluation of local recurrence	Technique; Local recurrence (if yes: Maximum diameter)
Physical examination^a^	Palpable breast tumour (if yes: size, skin infiltration, inflammatory carcinoma, satellite lesions); Palpable axillary nodes (if yes: size); Palpable supraclavicular nodes (if yes: size); Node staging
Acute and chronic toxicity	CTCAE term; Grade; Start date; Stop date; Status (recovered w/o sequels; death)

*eCRF* electronic case record form, *OSNA* One-Step Nucleic Acid Amplification, *TTL* total tumour load, *SLN* sentinel lymph node, *CTCAE* Common Terminology Criteria for Adverse Events

^a^Physical examination is conducted at follow-up visits. It is also addressed at baseline and radiotherapy sessions to confirm the compliance of eligible criteria. If suspicious LNs are detected, the patient will discontinue the study

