### Endpoints

#### Primary endpoint

The primary endpoint is the non-inferiority of incidental irradiation of axillary nodes in contrast to intentional irradiation, in terms of the 5-year DFS of patients diagnosed with early-stage breast cancer with limited involvement of the SLN treated with breast-conservative surgery without axillary lymphadenectomy.

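### The instruction that a patient with suspicious lymph nodes leaves the study is not limited to the time before randomisation; applied at follow-up with censoring, it could bias the trial towards non-inferiority

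*Protocol article*

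**What the plan says.** Footnote a is attached to the physical-examination panel of Table 2 (Data collection) and has three sentences:

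- The first places the examination at the scheduled visits after treatment.
- The second adds two further occasions and gives their purpose: "It is also addressed at baseline and radiotherapy sessions to confirm the compliance of eligible criteria".
- The third sets out the consequence of a nodal finding: "If suspicious LNs are detected, the patient will discontinue the study".

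The third sentence does not say which examinations it covers. Nor does it say whether a patient who leaves is counted as an event, censored or followed further.

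Other parts of the article treat nodal disease after randomisation as an outcome:

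- The Follow-up section states: "In each visit, a physical examination and recurrence assessment will be performed". Table 1 schedules both at 13 visits, from month 1 to month 60.
- Table 2 collects palpable axillary and supraclavicular nodes with their size, node staging, and an item that begins "Regional recurrence (If yes: nodal level".
- Secondary endpoints include loco-regional recurrence over the 5 years.
- The primary endpoint is non-inferiority "in terms of the 5-year DFS of patients diagnosed with early-stage breast cancer with limited involvement of the SLN".
- Under Statistical analysis, the confirmatory analysis uses the ITT set, which "includes all randomized patients regardless of whether the treatment or follow-up are accomplished".

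**The concern.** Before randomisation, a suspicious node is a reason not to enrol. After randomisation it may be a regional failure, which is an outcome of this trial. The footnote applies one instruction to both situations.

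The axillary nodes are where the two arms differ. The incidental arm has no treatment planning for nodal areas, so the excess that the trial must rule out would plausibly appear there first. The annual imaging panel is labelled for local recurrence. Palpation is therefore the scheduled examination that specifically records axillary and supraclavicular nodes.

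If patients leave at the point of suspicion and are censored, the censoring is related to the outcome. Later confirmation, distant recurrence and death would also be lost. Keeping such a patient in the ITT set does not restore an event that nobody observed. The trial is open-label, so the threshold for calling a node suspicious could differ by arm, and with more than 40 sites an ambiguous instruction can be applied in different ways.

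**Working it through.** **Inputs from the article (Sample size estimation; Study design; Dose prescription).** 1,400 patients allocated 1:1, so 700 per arm. Control 5-year recurrence rate 15%. Margin 5%, read here as 5 percentage points, so 15% against 20%. Dropout 5% per year. Power 80%. Breast radiotherapy lasts 3 to 5 weeks.

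**Assumptions.** The article states no alpha, so one-sided 5% and 2.5% are both shown. Nodal failure rates and the number of patients affected are not given and are varied. Event times and dropout are taken as exponential, and a confirmed regional recurrence as a disease-free survival (DFS) event.

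**1. The plan's own sample size.** Per arm, n = 2 × 0.85 × 0.15 × (1.645 + 0.842)² / 0.05² = 631, or 1,262 in total at one-sided 5%. Allowing for dropout gives 1,422 (inflating for lost events) or 1,438 (Greenwood variance at 5 years), both within 3% of 1,400. One-sided 2.5% gives 1,602 without dropout and about 1,805 to 1,832 with it. The stated size therefore fits one-sided 5% better. It is not in dispute and only sets the scale.

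**2. Standard error of the 5-year difference.** With event hazard λ = −ln(S)/5 and total hazard t = λ + 0.05, the per-patient variance of the Kaplan–Meier estimate is S² × (λ/t) × (exp(5t) − 1).

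- S = 0.85: λ = 0.0325, t = 0.0825, variance 0.1453.
- S = 0.80: λ = 0.0446, t = 0.0946, variance 0.1826.
- SE = √[(0.1453 + 0.1826)/700] = 0.02165, or 2.165 points.

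**3. Effect of removing part of the excess.** Let the true excess equal the margin, and let r be the net number of points removed from it (removals in the incidental arm minus removals in the control arm). Then P(declare non-inferiority) = Φ(r/2.165 − z).

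| Net removal r | One-sided 5% (z = 1.645) | One-sided 2.5% (z = 1.960) |
|---|---|---|
| 0 | 5% | 2.5% |
| 1 point (7 of 700) | Φ(−1.183) = 11.8% | Φ(−1.498) = 6.7% |
| 2 points (14 of 700) | Φ(−0.721) = 23.5% | Φ(−1.036) = 15.0% |

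**4. A second model with removals in both arms.** True failure is 15% against 20%. Nodal failures are assumed to be 2 points in control and 5 in the incidental arm, so 3 of the 5 excess points are nodal. A fraction f of nodal failures is censored at suspicion. The margin as a hazard ratio is ln 0.80 / ln 0.85 = 1.373. For f = 100%, the observed rates are 1 − 0.85^(13/15) = 13.1% and 1 − 0.80^(15/20) = 15.4%, a difference of 2.3 points.

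| f | Apparent difference | Hazard ratio | False non-inferiority, one-sided 5% | One-sided 2.5% |
|---|---|---|---|---|
| 25% | 4.3 points | 1.33 | 7.7% | 4.1% |
| 50% | 3.7 points | 1.29 | 11.6% | 6.6% |
| 100% | 2.3 points | 1.19 | 24.5% | 15.7% |

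A simulation of 20,000 trials agrees. Over control nodal rates of 1–3%, nodal excesses of 2–5 points and f of 25–100%, the false rate runs from 6.1% to 60.0% at one-sided 5%, and from 3.1% to 47.5% at one-sided 2.5%. With f = 0 the simulated rates are 5.2% and 2.6%, which is nominal.

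**5. The narrow reading: radiotherapy sessions only.** Three to five weeks is 3/260 to 5/260, or 1.2% to 1.9%, of the 5 years. At the control hazard, 1,400 × (1 − exp(−0.0325 × weeks/52)) gives 2.6 to 4.4 expected DFS events of any type in both arms together. The net difference between arms in nodal events would be smaller still, so the effect on the primary comparison is negligible.

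**The case against.** A reader might infer that the plan orders nodal failures found at follow-up to be taken out of the primary endpoint. The article does not support that, for these reasons:

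- The sentence directly follows the one that ties baseline and radiotherapy examinations to eligibility, so its natural antecedent may be that check alone.
- The fields for palpable nodes, node staging and regional recurrence by level, and the recurrence assessment at every visit, make most sense if nodal findings at follow-up are outcomes to be recorded.
- Nothing says that a patient who leaves is censored. Regional recurrence could be recorded at the same visit as the examination, and the event would then be captured before she left.
- Reasons for discontinuing follow-up must be reported, so affected patients could be identified.
- The ITT wording already anticipates incomplete follow-up. Lost follow-up would be a missing-data weakness, not a formal contradiction of the analysis set.
- Nodes palpable during radiotherapy more plausibly reflect disease present before randomisation, roughly balanced between arms.
- The instruction applies to both arms, so only the net difference matters, and that number is assumed.

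All of this stands, and it makes the point conditional. Three things remain. Even the eligibility reading reaches randomised patients, because radiotherapy sessions come after randomisation. The wording does not exclude follow-up visits. A node that is suspicious but not yet confirmed may not be recorded as a recurrence before the patient leaves.

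**Conclusion.** The point holds in conditional form. The footnote permits the bias, but the article does not establish that it occurs. Bias towards non-inferiority requires that the sentence is applied at follow-up visits, that patients are censored before confirmation, and that more nodal failures are lost in the incidental arm than in the control arm.

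Under those conditions, a net loss of only 7 to 14 of 700 incidental-arm patients raises the false non-inferiority rate from 5% to about 12–23.5% (from 2.5% to about 7–15% at one-sided 2.5%). These figures illustrate sensitivity and are not estimates, because the article gives neither the number affected nor the alpha. If the sentence reaches only radiotherapy sessions, the effect is negligible.

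The article does not show that anyone has left under this sentence. Its status report gives 451 patients recruited and 13 recurrence events, with no count of discontinuations on this ground.

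**What to change.** Reconcile footnote a with the Follow-up section, the secondary endpoints and the ITT analysis:

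1. Limit study discontinuation for suspicious nodes to findings before randomisation.
2. State that every randomised patient stays in recurrence and vital-status follow-up and in the ITT set, whatever is found on examination. Record the finding in the existing regional-recurrence field, and count a confirmed nodal recurrence as a DFS event.
3. Check whether any randomised patient has left the study under this sentence and, if so, retrieve her recurrence and vital-status outcomes.

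The cost is a short change to the protocol and the eCRF instructions plus one query of the discontinuation records. The sample size stays at 1,400. Follow-up that is not collected now may not be recoverable later. The clinical management of suspicious nodes is outside this point.
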